#### Primary analysis

##### Primary safety and efficacy endpoints

Mixed effect generalized linear (logistic) models will be implemented in order to estimate the effect of intervention on safety (clinical failure) and efficacy (antibiotic prescription). The models will contain a random cluster level effect and a period specific fixed effect. Both intervention effects will be expressed in an odds ratio (OR) scale. A lower one-sided 95% confidence interval will be used in order to test effect significance for the safety outcome, reached when the upper bound of the interval is smaller than the non-inferiority margin (translated into the OR scale); a two-sided 95% confidence interval will be used to test effect significance for the efficacy outcome, reached when the interval does not contain the value of one.

#### Secondary analyses

*The effect on bothersomeness of community-acquired pneumonia-related symptoms* on day 7, day 28, and day 90 will be evaluated by comparing the number of points on the CAP symptom questionnaire between study groups by linear mixed effect models containing a random cluster level effect and a period-specific fixed effect. The effect on the *duration of ED stay will be evaluated* using survival models including frailty term for the cluster effect (Coxmodel).

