### Eligibility and exclusion criteria

All adult patients, aged 18 or older, presenting with an acute LRTI, are screened for inclusion by study nurses (SN) during working hours (weekdays 8am–5pm). Acute LRTI is defined, according to the European Society of Clinical Microbiology and Infectious Disease (ESCMID) guidelines [4], as an acute illness of less than 21 days, featuring at least one lower respiratory tract symptom, i.e., cough, sputum, dyspnea, or chest pain with no alternative explanation. Every consecutive patient meeting the inclusion and exclusion criteria detailed in Table 2 and providing a signed informed consent is included. SNs and/or physicians are responsible for collecting written patient’s informed consent for each participant.

**Table 2 Tab2:** Inclusion and exclusion criteria

Inclusion criteria	Exclusion criteria	
Patients aged 18 years or more	Previous receipt of a quinolone, macrolide, or ceftriaxone or more than one dose of any other antibiotic within 72 h prior to enrolment (excepted prophylactic antibiotics or antibiotics given for urinary tract infection)	
Acute LRTI (acute illness, less than 21 days, with at least one lower respiratory tract symptom, i.e., cough, sputum, dyspnea, chest pain, and no alternative explanation)	Acute care hospital stay in the previous 14 days	
At least one of the following clinical criteria:	Cystic fibrosis	
o Focal abnormal auscultation (decreased breath sounds, crackles, bronchial breath sounds)	Severe COPD (≥GOLD 3 or if not available, as a proxy: exacerbation treated with antibiotics during the last 6 months)	
o Fever (documented temperature ≥ 38°C in the last 24 h, including self-measured temperature ≥ 38°C)	Severe immunodeficiency (drug-induced neutropenia with <500 neutrophils/mm^3^, HIV infection with CD4<200 cells/mm^3^, solid organ or bone marrow transplant recipient, prednisone ≥ 20 mg/day for >28 days)	
o Tachypnoea (respiratory rate ≥ 24/min)	Initial admission of the patient in the intensive care unit	
o Tachycardia (heart rate ≥ 100/min	Microbiologically documented infection with SARS-CoV-2 (in the last 10 days)	
	Lack of decision-making capacity	

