### Endpoints

The primary safety endpoint is the proportion or patients with clinical failure by day 28. Clinical failure is defined as death from any cause, secondary intensive care unit (ICU) admission for any cause, secondary admission to hospital (excluding elective admission), hospital re-admission after index hospital discharge (excluding elective admission), or local complications due to the LRTI (empyema, lung abscess).

The primary efficacy endpoint is the proportion of patients prescribed an antibiotic by day 28. Table 4 summarizes the secondary and exploratory endpoints.

**Table 4 Tab4:** Study endpoints

Primary safety endpoint	
Proportion of patients with clinical failure by day 28, defined as: death from any cause, or secondary ICU admission for any cause, or secondary admission to hospital (excluding elective admission), or hospital re-admission after index hospital discharge (excluding elective admission), or ­ local complications due to the LRTI (empyema, lung abscess)	
Primary efficacy endpoint	
Proportion of patients prescribed an antibiotic by day 28.	
Secondary endpoints	
Number of points on the CAP symptom questionnaire as a surrogate marker of quality of life on days 7, 28, and 90 in each study group.	
Duration of ED stay in each study group.	
Rate and duration of hospitalization in each study group	
Proportion of patients prescribed an antibiotic for a new respiratory infection in each study group between days 28 and 90.	
Proportion of patients with antibiotic-related side effects and *C. difficile* infections in each study group.	
Identification of barriers and facilitators to the implementation of the algorithm with patients and ED physicians involved in the study.	
Quality-adjusted life years (QALYs), derived from responses to the EQ-5D questionnaire, in each group	
Measurement of the incremental cost-effectiveness ratio (ICER) of the intervention as compared to usual care.	
Advanced automatic LUS image analysis method using machine learning to assist in LUS diagnosis and risk stratification.	
Proportion of physician reaching proficiency in LUS image/video acquisition and interpretation after the training module.	
Sensitivity, specificity, and area under the ROC of physician “gestalt” and Van Vugt prediction score for CAP diagnosis.	
Exploratory endpoints	
Proportion of LRTIs patients with a documented bacterial, viral, and mixed infection.	
Nasopharyngeal microbiome in adult Swiss patients with LRTIs.	

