### At enrolment

Study data will be collected (from the patient and/or the medical file) by the study team in an eCRF developed on the electronic data collection (EDC) system REDCap®, hosted at Lausanne University Hospital [35, 36]. Data collected at inclusion includes demographic characteristics, comorbidities, symptoms and their duration, vitals and clinical signs, diagnostic tests required by the ED physician for LRTI management of the included patients (chest X-ray, CT-scan, LUS, CRP, PCT, white blood cell count, blood chemistry, blood gas, microbiology tests), destination on ED discharge, and antibiotic prescription. During the intervention period, the data collection will also include PCT results and LUS interpretation. Furthermore, physicians will record all their LUS images and videos following the aforementioned procedure in a secured drive.

A collection of biological samples (blood, respiratory, and urine) is performed parallel to the intervention trial as a study data-linked biobank. This includes a collection of nasopharyngeal and oral swabs, sputa if available, whole blood, plasma, PAXgene™ blood RNA system tubes, and urine samples at inclusion in all study centers. Furthermore, urine samples are collected on day 7 in the University Hospital of Lausanne and the Cantonal Hospital of St Gallen.

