### Statistical analyses

#### Datasets to be analysed, analysis populations

All analyses will be carried out in the primary analysis population, which includes all enrolled patients following an intention-to-treat principle. Any missing data at the enrolment visit due to incomplete documentation of the pre-assigned components of the algorithm will lead to the patient being assigned to the intention-to-treat analysis. Patients who are lost to follow-up will be replaced by additional patients’ inclusion as mentioned in the sample size (10% additional patients to compensate for loss to follow-up). Patients lost to follow-up will not be included in the analysis (complete case analysis). The primary efficacy and safety analyses will be repeated on the per-protocol population. The per-protocol population includes all patients who received all components of the PLUS algorithm without overruling on admission and 6–24 h later.

Stratified analyses will be done for severe LRTIs and non-severe LRTIs based on CRB-65 and PSI scores.

A sensitivity analysis will include patients who received a component of the intervention (PCT or LUS) while in the “usual care group” to evaluate if there is still an impact of the intervention when these tests are part of the usual care.

Additional analysis adjusting for patient level confounding factors (age, asthma, chronic obstructive pulmonary disease, CRB-65, and PSI score) in the intention-to-treat analysis will be done for both co-primary endpoints.

We will develop a detailed data analysis plan for secondary, subgroup, stratified, and sensitivity analyses. All analyses will be done with R Statistical Software.

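### The CAP symptom-score models name no baseline covariate, although symptoms and symptom duration are recorded at inclusion and patients enter at widely different stages of illness

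*Protocol article*

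**What the plan says.** All references are to the protocol article.

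- **Endpoint (Endpoints, Table 4).** The first secondary endpoint listed is "Number of points on the CAP symptom questionnaire as a surrogate marker of quality of life on days 7, 28, and 90", compared between study groups.
- **Model (Secondary analyses).** The score is to be compared "by linear mixed effect models containing a random cluster level effect and a period-specific fixed effect". No baseline covariate is named. The text does not say whether the three days are fitted together or one at a time.
- **Adjustment (Datasets to be analysed, analysis populations).** An adjusted analysis with age, asthma, COPD, CRB-65 and PSI is planned "in the intention-to-treat analysis will be done for both co-primary endpoints". The list contains neither symptoms nor symptom duration, and the symptom score is not among the outcomes covered. The same section promises a detailed analysis plan for the secondary analyses.
- **Baseline data (At enrolment).** The items collected at inclusion include "demographic characteristics, comorbidities, symptoms and their duration, vitals and clinical signs".
- **Entry window (Eligibility and exclusion criteria).** Acute LRTI is defined "as an acute illness of less than 21 days".

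**The concern.** A symptom score in an acute illness depends heavily on how far the illness has run and how bad it was at the start. With entry allowed up to illness day 20, the day-7 score can fall anywhere from about illness day 7 to day 27. That spread sits in the residual variance unless the model accounts for it.

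There is also a question of bias. The period effects remove calendar trends that the centers share. They do not remove a change in who is enrolled when one center moves to the intervention. The trial is open-label, the switch dates were disclosed to centers before the study began (Blinding), patients are recruited after that, and only nine clusters are randomized. If patients enrolled after a switch are systematically earlier or later in their illness, the named terms leave that difference in the estimated effect.

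At stake is a patient-reported comparison for an algorithm that withholds antibiotics. The score also enters the condition-specific cost-effectiveness ratio, in CHF per point on the questionnaire (Cost-effectiveness of the intervention), so noise or bias would carry over to that result.

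**Working it through.** The protocol gives no SD, target difference or power for the symptom score, so there is no stated figure to reproduce. Results are in SD units of the score.

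**Inputs from the protocol (Sample size).** 9 clusters, 10 periods, one cluster switching per step, 15 evaluable patients per cluster-period. The ICC of 0.2 is stated for clinical failure and is borrowed here; 0.01 and 0.05 are added as a range.

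**Assumed inputs, not in the documents.** Correlation r between baseline symptoms or duration and the later score: 0.1 to 0.5. Within-patient correlation w between the three scores: 0.2 to 0.7. Baseline shift at the switch: 0.1 to 0.2 SD.

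**Step 1, precision of one day's model.** The standard stepped-wedge generalized least squares variance was used, with period fixed effects and a random cluster effect. Each cluster's ten period means have covariance ICC·J + [(1 − ICC)/15]·I, where J is the all-ones matrix and I the identity. Adjustment multiplies the residual part (1 − ICC) by (1 − r²).

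| ICC | SE unadjusted | SE at r = 0.2 | SE at r = 0.3 | SE at r = 0.5 |
|---|---|---|---|---|
| 0.01 | 0.0824 | 0.0810 (−1.7%) | 0.0792 (−3.9%) | 0.0729 (−11.6%) |
| 0.05 | 0.0889 | 0.0873 (−1.9%) | 0.0851 (−4.3%) | 0.0778 (−12.6%) |
| 0.2 | 0.0844 | 0.0827 (−2.0%) | 0.0806 (−4.5%) | 0.0733 (−13.2%) |

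At r = 0.1 the reduction is about 0.5%.

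**Step 2, what a systematic shift would do.** If the baseline variable differs by d SD between intervention and control enrolment, beyond what cluster and period explain, the unadjusted effect moves by about r × d.

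- Low end: 0.3 × 0.1 = 0.03 SD, which is 0.03/0.0889 = 0.34 to 0.03/0.0844 = 0.36 of a standard error.
- High end: 0.5 × 0.2 = 0.10 SD, which is 0.10/0.0889 = 1.12 to 0.10/0.0844 = 1.18 standard errors.

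This shows what follows if such a shift occurs. Nothing in the documents says that it does.

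**Step 3, the three scores.**

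- *One model per day:* each patient contributes one score to each fit, so no patient term is needed.
- *One joint model with only the named terms:* the average of a patient's three scores has residual variance proportional to (1 + 2w)/3, while the model takes it as 1/3. The true SE of an effect averaged over days is then about √(1 + 2w) times the reported one: √1.4 = 1.18 at w = 0.2, √2 = 1.41 at w = 0.5, √2.4 = 1.55 at w = 0.7. The harm here is a reported SE that is too small, not a loss of precision.

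**The case against.** The strongest reply is deferral. The article promises a detailed analysis plan for the secondary analyses, and covariates and the handling of repeated scores are what such a plan settles. The model sentence says what the models contain; it does not say they contain nothing else. This stands in part: a reader might infer that the model is closed to further terms, and the text does not support that. What deferral does not remove is that the article already names the model terms for this endpoint and already confines patient-level adjustment to the co-primary endpoints. A later plan that follows this text would carry both forward.

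A reader might also infer that the absence of a patient-level term is an error in itself. It is not. The sentence speaks of models in the plural and the endpoint is listed by day, so one model per day is at least as natural a reading, and that needs no such term. Nor does the protocol define an effect averaged over the three days.

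Third, the gain may be small. No baseline CAP questionnaire score is named in the endpoints or the enrolment data, and the schedule of assessments is not readable in the available text. The known candidates are symptom items and duration from the case report form, whose correlation with the later score is unknown. This stands, and it is why the size is given as a range that begins near zero.

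Finally, a reader might infer that the unadjusted estimate is biased. Chance imbalance is already reflected in its standard error. Systematic imbalance is possible under open-label recruitment, but study nurses screen patients and every consecutive eligible patient who consents is to be included, which works against it. Safety is carried mainly by the co-primary clinical-failure endpoint, for which adjustment is planned.

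**Conclusion.** The point holds in a limited form. The symptom-score models are described without any baseline covariate, and the adjusted analysis leaves this endpoint out, while clearly relevant baseline data are collected on an outcome measured at very different stages of illness. The unadjusted model remains valid for chance imbalance; it is less efficient than it could be and offers no protection against a systematic shift in illness stage.

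Under the assumed correlations the loss is modest: 4–5% of the SE at 0.3, 12–13% at 0.5, and negligible at 0.2 or below. The protection against a shift at the switch matters only if one occurs. Whether the days are modelled jointly or separately is a matter for clarification. An SE understated by a factor of about 1.2 to 1.55 would arise only in a joint fit without a patient term, with an averaged effect and within-patient correlation of 0.2 to 0.7.

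**What to change.** In Secondary analyses, and in the promised plan for secondary analyses:

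1. Add inclusion symptoms and symptom duration as fixed covariates in the symptom-score models, together with age, COPD and CRB-65, which are already listed for the co-primary adjusted analysis. Keep the random cluster effect and the period fixed effects.
2. State whether days 7, 28 and 90 are fitted separately or jointly. If jointly, include group-by-day terms and a patient random intercept. If separately, no patient term is needed.
3. State how missing covariate values are handled.

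The cost is a change of wording, a little more analysis work and the handling of any missing covariate values. No new data collection is needed.

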## Methods: Assignment of interventions

### Randomization, allocation, and timeline

The unit of randomization will be the nine centers, representing the clusters. In accordance with the stepped wedge cluster randomization design, after a common baseline 10-week-period of usual care (all patients included in the control group), one center will switch to the intervention phase (patients included in the intervention group) at each pre-determined time period (every 10 weeks, which corresponds to a step). All study centers will be in the intervention period for the last 10 weeks of the study (Table 5). The total duration of the study will be 113 weeks, including the follow-ups. The sequence of rolling into intervention (from control period to intervention period) was randomly generated between study centers using the web-based randomizing program: random.org. The nature of the study intervention precludes randomization at the patients’ level. Indeed, the intervention is targeting the decision-making process of the clinician and might contaminate the usual care group in case of patients’ randomization. Figure 3 represents the CONSORT flow diagram of the PLUS-IS-LESS study following SPIRIT guidance.

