### Analyses

#### Sample size

The study is designed to demonstrate non-inferiority of the intervention in term of clinical failure occurrence and superiority in term of reducing antibiotic prescription. We plan to include 1530 patients in 9 study centers. Every study center will recruit 170 patients over about 2 years.

According to a stepped-wedge cluster-randomized design with a control period plus nine switch periods (steps) and the same number of clusters (one switch to intervention at each step), a mean number of 15 patients per unit and per time period will guarantee a 80% power (one-sided type I error *α* = 0.05) to prove non-inferiority regarding clinical failure (safety), if the proportion of clinical failure is 20% in both groups, with a non-inferiority margin of 10%, and assuming an intra-cluster correlation (ICC) of 0.2 and a coefficient of variation (cv) of the number of patients across units of 0.3. With 15 patients per unit and per time period, we would obtain a total sample size of 1350 (15 × 9 × (9+1)) patients. Further considering a 10% of lost to follow-up, we anticipate 15/0.9 = 17 patients per unit and per time period, leading to our final sample size of 1530 (17 × 9 × (9+1)) patients.

In our calculation, the ICC of 0.2 is based on results of a previous trial, the UltraPro trial [37]. The coefficient of variation of 0.3 in the number of patients between units is intended to allow for some variability between centers in the number of patients recruited. With an average number of 15 patients per cluster and per step, this corresponds to admitting that 95% of the clusters will recruit between 6 and 24 patients per step (between 60 and 240 in total). Correcting for 10% loss to follow-up, the same range will be between 67 and 267.

Of note, the 10% non-inferiority margin is supported by US FDA recommendations for anti-infectious trials assessing clinical success of a new treatment [38]. Sample size calculation with a 5% margin would lead to 5100 patients jeopardizing the feasibility of the trial.

This sample size in the framework of a stepped-wedge design guarantees a power of more than 90% to prove superiority regarding antibiotics prescription (efficacy), if the proportion of antibiotics prescribed is 0.65 in the control group and 0.5 in the intervention group (*α* = 0.05).

The sample size was calculated with R software, based on the manuscripts by Hemming et al. [39] and Harrison et al. [40].

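### The Cox model stated for duration of ED stay names a cluster frailty but no period term, so fitted as written it would pass calendar trend into the intervention effect

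*Protocol article*

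**What the plan says.** The protocol article describes three models for patient outcomes.

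- **Co-primary endpoints** (Primary safety and efficacy endpoints): logistic mixed models. "The models will contain a random cluster level effect and a period specific fixed effect".
- **CAP symptom score** (Secondary analyses): "linear mixed effect models containing a random cluster level effect and a period-specific fixed effect".
- **Duration of ED stay** (Secondary analyses, next sentence): analysed "using survival models including frailty term for the cluster effect (Coxmodel"). No period term is named.

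The rollout is set out under Randomization, allocation, and timeline. "The unit of randomization will be the nine centers, representing the clusters". They switch one at a time "after a common baseline 10-week-period of usual care", with a switch "every 10 weeks, which corresponds to a step". At the end, "All study centers will be in the intervention period for the last 10 weeks of the study". The Sample size section gives the same layout: "with a control period plus nine switch periods (steps) and the same number of clusters (one switch to intervention at each step").

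Two other places bear on the point. The Discussion says the design makes it possible to control for seasonality. The section on analysis populations promises a separate detailed plan for the secondary analyses, which is not shown.

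**The concern.** In a stepped wedge, intervention status and calendar time are tied together by design. A cluster frailty absorbs differences between centers but does nothing about time. It also moves the estimate toward the within-center contrast of earlier against later weeks, where the confounding with time is strongest. Only a time term separates the two.

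Of the three models, the one for ED stay is the only one that names no such term. If it is fitted as stated, part of any movement in ED stay between late 2022 and late 2024 that is unrelated to the algorithm would be read as its effect. The confidence interval would also be narrower than the design supports, because its width would assume that there is no time trend.

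**Working it through.** **Layout.** The protocol gives no figure for time confounding and no power for ED stay, so only its layout can be reproduced. 15 × 9 × 10 = 1350; 15/0.9 = 16.7, rounded to 17; 17 × 9 × 10 = 1530, as stated. Ten periods of 10 weeks also fit the recruitment window of 5 December 2022 to 3 November 2024, about 100 weeks.

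**Step 1: gap in calendar time within a center.** Number the periods 1 to 10. A center whose last control period is *i* (*i* = 1 to 9) has
- mean control period (i + 1)/2
- mean intervention period (i + 11)/2
- difference (i + 11)/2 − (i + 1)/2 = 5 periods = 50 weeks, for all nine centers.

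**Step 2: gap ignoring center.** There are 45 control and 45 intervention cells. Their period numbers sum to 165 and 330. The gap is 330/45 − 165/45 = 3.67 periods, or 36.7 weeks.

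**Step 3: what a model with a cluster effect and no period term picks up.** The linear analogue is generalized least squares on cell means, with covariance (1 − ρ)/m · I + ρ · J within a center (m = 17 per cell). The design matrix is an intercept plus the intervention indicator. The outcome is a pure linear trend of one unit per period, with no intervention effect. The coefficient on intervention is the multiple of the per-period drift that passes into the effect:

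| ICC (ρ) | multiple of drift | weeks of trend |
|---|---|---|
| 0 | 3.67 | 36.7 |
| 0.005 | 4.18 | 41.8 |
| 0.01 | 4.41 | 44.1 |
| 0.05 | 4.82 | 48.2 |
| 0.1 | 4.91 | 49.1 |
| 0.2 | 4.96 | 49.6 |

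With 15 per cell the value at ICC 0.2 is 4.95. The protocol's ICC of 0.2 is a planning value for clinical failure; none is given for ED stay, so the whole range applies.

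**Step 4: illustration under assumed drift.** The drift rates are assumptions.
- 1% in the discharge hazard per 10 weeks: 3.67 × 1% = 3.7% to 4.96 × 1% = 5.0%.
- 2% per 10 weeks: 3.67 × 2% = 7.3% to 4.96 × 2% = 9.9%.

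**Step 5: non-linear time patterns.** In the same calculation an annual cycle passes roughly 0.4 to 0.5 of its amplitude at the least favorable phase. The 100 weeks do not balance the seasons between conditions.

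**Step 6: check with a Cox model.** Simulation with 9 × 10 × 17 patients, true hazard ratio 1, an assumed center SD of 0.3 on the log hazard and 1000 runs per row. Centers were entered as fixed terms; a smaller run with a gamma frailty gave similar hazard ratios.

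| assumed fall in discharge hazard per year | HR, no period term | type I error, no period term | type I error, period added |
|---|---|---|---|
| none | 1.00 | 5.6% | 6.1% |
| 5% | 0.95 | 14% | 5.2% |
| 10% | 0.90 | 40% | 5.5% |
| 20% | 0.81 | 94% | 4.9% |

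The hazard ratios agree with 50 weeks of trend: 0.95^(50/52) = 0.952, 0.90^(50/52) = 0.904, 0.80^(50/52) = 0.807. With period added, the simulated null hazard ratio is 0.99 to 1.00 in every row. The standard error of the log hazard ratio rises from about 0.060 to about 0.090.

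**The case against.** The strongest objection is that the sentence is not a full specification. It says what the survival model includes, and it does not name the intervention term either, which must be present. The article defers detail on secondary analyses to a separate plan, and its Discussion shows an intention to control for seasonality. On that reading period was left out for brevity. This part stands: the text omits period and does not exclude it. A reader might infer that the authors decided to drop period from this model, and the document does not support that.

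What does not stand is that the omission is therefore ordinary missing detail. The article chose to state this model. The sentence directly before it and the primary-analysis section both name cluster and period together, while this one names cluster alone. Neither the deferral nor the Discussion supplies the missing term, and control for seasonality is delivered only by a model that contains time.

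The size is also open to challenge. The multiplier depends on an ICC that is not given for ED stay, and no drift is documented. Without drift there is no bias (simulated type I error 5.6%). A reader might infer that every change in crowding, staffing or season would be reported in full as an effect of the algorithm. That goes too far: the multiple of about 3.7 to 5 applies to a sustained linear drift, and a seasonal cycle passes only about half of its amplitude or less.

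**Conclusion.** The point holds as an inconsistency between stated models. The ED-stay model as written lacks the period term that the design requires and that the other two models name. Fitted that way, it would carry about 37 to 50 weeks of any linear trend into the intervention effect, depending on the between-center variance, and would overstate precision.

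The 50-week within-center gap is exact for the stated rollout. The percentage effects are illustrations that rest on assumed drifts. Confidence is moderate, because the unseen analysis plan may already contain the term.

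The reach is one secondary endpoint. It would be wrong to infer that the co-primary results are at risk, since those models include period. Nor does one sentence support a claim that time is handled badly throughout the plan.

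**What to change.** State that the Cox model for duration of ED stay includes period, either as a fixed effect or by stratifying the baseline hazard by period, and keep the cluster frailty. This brings it into line with the symptom-score and co-primary models and with the Discussion's statement on seasonality.

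The change is one term in one model and needs no new data. Its cost is precision: in the simulation the standard error of the log hazard ratio goes from about 0.06 to about 0.09. The smaller value is valid only if ED stay has no time trend.
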